## 2. Methods

### 2.1. Study design

This study was designed as a single-blind, pilot, randomized controlled clinical trial. This protocol was developed in accordance with the Standard Protocol Items: Recommendations for Interventional Trials (SPIRIT) guidelines (S1 Table) and the TIDier checklist (S2 Table). We designed a stratified random sampling protocol and will conduct a two-arm randomized controlled trial comparing conventional rehabilitation alone with conventional rehabilitation combined with additional in-bed self-exercises based on EMG sensor feedback (Fig 1). Participants will be enrolled from a tertiary hospital and a rehabilitation hospital. This study is a pilot, randomized controlled clinical trial investigating the feasibility and safety of in-bed self-exercises and aims to recruit at least 20 participants. Assuming a 15% loss to follow-up, the required sample size was set at 24 patients (12 patients per group) to be recruited in this study. The study received approval from the Seoul National University Hospital Institutional Review Board (IRB No: D-2208-177-1354, September 21, 2023) (S1 File), and the protocol was registered and approved on the ClinicalTrials.gov (Trial record: NCT05820815).

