The primary outcome measure is the Pittsburgh Rehabilitation Participation Scale (PRPS). The PRPS is a clinician-administered instrument designed to assess the participation of patients in rehabilitation [29, 30]. It is rated on a scale of 1–6 to measure a patient’s effort and activity to participate in rehabilitation. The patient’s session participation and effort levels were assessed across six distinct categories, ranging from "none" to "excellent." The "none" category signifies that the patient either declined to participate in the entire session or did not engage in any exercises during the session. Conversely, the "excellent" category denotes that the patient actively participated in all exercises with maximal effort, successfully completing each exercise and displaying a keen interest in both the exercises and any future therapy sessions. The remaining categories describe varying degrees of participation and effort between these two extremes [30]. In the PRPS, there are three types of exercise sessions to be newly defined as follows: (i) a participating session, in which the number of contractions of target muscles is more than one; (ii) an effortful session, in which the amplitude of one or more target muscles during contractions is more than 20% of maximal voluntary isometric contraction; (iii) a successful session, a session in which the amplitude of one or more target muscles during contractions is more than 50% of maximal voluntary isometric contraction. The six categories of PRPS using the concept of participating, effortful, and successful sessions are defined as follows: (i) none, 0% of participating sessions; (ii) poor, <50% of participating sessions; (iii) fair, ≥50% of participating sessions and <50% of effortful sessions; (iv) good, ≥90% of participating sessions, ≥50% and <90% of effortful sessions; (v) very good, ≥90% of participating sessions, ≥90% of effortful sessions, and ≥90% of successful sessions; (vi) excellent, ≥90% of participating sessions, ≥90% of effortful sessions, ≥90% of successful sessions, and active involvement in establishing exercise plans for future sessions (Fig 9).

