### 2.7. Management

The researchers will ensure the protection of participant anonymity and the confidentiality of data related to individuals, safeguarding their identities and any identifying information. Clinical records, research instruments, or any documents containing participant data will be identified by a code instead of the participant’s name, even when submitted to regulatory institutions or sponsors. The researchers will secure the records of the participants and maintain the confidentiality of information regarding codes, names, and addresses, limiting access to only the researchers. All files will be stored in a dedicated, secure location within a single folder for this study.

Participation in this study is entirely voluntary, and non-participation will not impact the patient’s medical follow-up or the relationship between the team and the patient. Upon signing the consent form, patients may choose to withdraw from the study at any time without consequences regarding their treatment or follow-up at the institution.

The risks during the research are expected to be minimal. The evaluation may be temporarily halted to allow for necessary medical interventions. However, if discomfort persists, the participant will be excluded from the research, any collected data will be excluded from analysis, and the patient will not be reassigned to another group.

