### 2.8. Statistical methods

All statistical analyses will be performed for intention-to-treat and a per-protocol population. Descriptive statistics, including mean and standard deviation, median and range, or number and percentage, will be provided for all assessed outcomes. To investigate the effects of time and groups on outcome variables, a repeated measures design with a linear mixed model will be employed. The linear mixed model will include time (baseline, 3 weeks, and 12 weeks), group (control and intervention groups), and time*group interaction as fixed effects, while sex, height, and weight will be treated as random effects. Assumptions of normality, independence, and homoscedasticity will be checked to ensure the validity of the model. Effect sizes with 95% confidence intervals will be calculated. Missing data will be handled using multiple imputation or maximum likelihood estimation. A two-tailed approach will be used. The significance level will be set at p<0.05. All statistical analyses will be conducted using SPSS (version 25.0; IBM, Armonk, NY).

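### The general missing-data rule in section 2.8 allows participation to be imputed for patients who leave during the 3-week programme, which can overstate feasibility

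*Protocol article*

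**What the plan says.** All references are to the protocol article.

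- **Missing data (section 2.8).** "Missing data will be handled using multiple imputation or maximum likelihood estimation". No outcome is exempted. The same section states: "All statistical analyses will be performed for intention-to-treat and a per-protocol population". The model has three time points: baseline, 3 weeks and 12 weeks.
- **Primary outcome (section 2.5.1).** The lowest PRPS category, *none*, means that "the patient either declined to participate in the entire session or did not engage in any exercises during the session". The six categories are then graded by the percentages of participating, effortful and successful sessions. Less than half of sessions participating is *poor*. The session percentages are also secondary outcomes.
- **Programme (section 2.4.2).** Self-exercise is prescribed for at least two sessions a day, five days a week, for three weeks. Therapists follow exercise frequency daily through their app.
- **Leaving the trial (sections 2.1 and 2.7).** The sample size is set "Assuming a 15% loss to follow-up". On withdrawal, "patients may choose to withdraw from the study at any time without consequences regarding their treatment or follow-up at the institution"; this sentence concerns care and does not say how the data are treated. Section 2.7 adds that a participant whose discomfort persists is removed and that the data already collected are left out of the analysis.

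**The concern.** The primary outcome measures whether patients exercise. For a balance or strength score, a missed assessment hides a value that exists, and multiple imputation or likelihood estimation is a reasonable way to deal with it. For a participation score, absence from the programme is itself information about the outcome.

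A patient who withdraws, is lost or is excluded before week 3 may have no 3-week PRPS. Under the general rule that value may be treated as missing. Both named methods, as usually applied, assume missingness at random and so borrow from patients who stayed. If the patient left because the exercises were unacceptable or too hard, the reason for the gap is the quantity being measured. The result then describes participation had everyone continued, whereas a feasibility study asks how much of the prescribed programme was done.

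The exclusion in section 2.7 is a second route to the same problem. Section 2.6 lists discomfort at the sensor sites as a possible adverse event, so those removed may include patients who could not tolerate the device. An intention-to-treat analysis would have to omit them or impute them without their own early sessions.

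**Working it through.** **The plan's own figure.** Section 2.1 "aims to recruit at least 20 participants" and allows for 15% loss: 20 / 0.85 = 23.5, rounded up to 24, or 12 per group. This reproduces. Fifteen per cent of 12 is 1.8 patients per arm. That figure is loss over the whole 12 weeks; the documents do not say how much falls within the 3-week programme.

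**Prescribed sessions (section 2.4.2).** 2 × 5 × 3 = 30 as a minimum, 10 per week.

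**Illustration.** Assumed: 2 of 12 intervention patients leave after week 1, having done 9 of 10 sessions; continuers perform 90%; missing sessions are predicted at the continuers' rate.

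- Unperformed sessions counted as not done: 9 / 30 = 30%, which is *poor* (category 2).
- Remaining 20 sessions imputed at 90%: (9 + 18) / 30 = 27 / 30 = 90%.
- Difference per leaver: 60 percentage points. On the arm mean: 60 × 2/12 = 10 points.
- PRPS: 90% participation does not fix the category. With fewer than half of sessions effortful it is *fair* (3). With more effortful and successful sessions it is *good* (4) or *very good* (5). The gap from category 2 is therefore 1 to 3 categories, and the shift in the arm mean is 1 × 2/12 = 0.17 to 3 × 2/12 = 0.5 points.
- With one such patient, the shift is 60 × 1/12 = 5 points of sessions and 1/12 = 0.08 to 3/12 = 0.25 PRPS points.

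**General form.** Let d be the share who leave, p the participation rate while exercising, and f the fraction of the programme completed before leaving. The arm mean is p if the remainder is imputed and (1 − d)p + dpf if it counts as zero. The overstatement is dp(1 − f).

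- Check against the illustration: 2/12 × 0.90 × 2/3 = 0.10.
- With d = 15% (the plan's loss figure, assumed here to fall entirely within the programme), p from 70% to 95% and f from 0 to 0.75, the overstatement runs from 0.15 × 0.70 × 0.25 = 2.6 points to 0.15 × 0.95 × 1 = 14.2 points.

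Whenever leavers would otherwise count as non-participating and are instead predicted at the continuers' rate, the difference is upward. Its size rests on assumed rates.

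**The case against.** A reader might infer that sections 2.5.1 and 2.8 contradict each other and that participation is certain to be inflated. The documents do not support that. Section 2.8 does not say that an unperformed session is missing data, and section 2.5.1 gives non-performance an observed value. The two can be read in sequence: the scale defines the value, and the missing-data rule applies only where none exists. Daily monitoring makes non-use visible. A patient who stops but stays in follow-up is scored low, with nothing to impute. All of this stands, and it confines the point to patients who withdraw, are lost or are excluded during the three weeks.

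The figures are also open to challenge. A patient lost between weeks 3 and 12 has complete session data, so the 15% cannot be read as early stopping. Imputation can use a patient's own earlier data, so prediction at the continuers' rate is an assumption. This too stands, and the sizes above are illustrations only. Good early sessions would not, however, remove the problem: the patient in the example did 9 of 10 before leaving.

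It can be said that scoring after withdrawal, and the denominator of the percentages, belong in an analysis plan that is not shown. As omissions they would be no finding. The point rests on what is stated: one rule, without exception, that reaches a primary outcome it does not suit.

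Finally, scoring zero after every departure is debatable. A patient removed for a recurrent stroke (an exclusion criterion in section 2.2) says little about whether the programme is acceptable. That is right, and the fix below allows for it.

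**Conclusion.** The point holds in a limited form. Section 2.8 allows the participation of patients who leave during the programme to be estimated from those who continued, although section 2.5.1 treats not exercising as non-participation. Feasibility can then be overstated; that it will be is not shown. With two of 12 leaving early, under the stated assumptions, the overstatement is about 10 percentage points of sessions and 0.17 to 0.5 PRPS points. It falls in proportion with fewer early leavers and is nil if nobody leaves during the three weeks. For clinical scales missed at 3 or 12 weeks, the rule is acceptable as it stands. With 12 patients per arm and feasibility as the stated aim, the wording should be corrected.

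**What to change.** In section 2.8:

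1. Limit multiple imputation and maximum likelihood to unobserved clinical assessments and to sessions lost through a logged sensor or app failure.
2. For PRPS and the session outcomes in the self-exercise arm, use the sessions prescribed for the 3 weeks as the denominator. Count unperformed sessions as non-participating, including those after stopping or withdrawal.
3. Report stops for reasons unrelated to the programme separately, and give an analysis of sessions up to the point of stopping as a sensitivity analysis.
4. Reconcile the exclusion of collected data in section 2.7 with the intention-to-treat analysis.

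The cost is a few sentences and a device-failure flag in the app log or case report form; the sample size stays at 24. The downside is that reported participation will be somewhat lower and that unrelated withdrawals count against feasibility in the main analysis, which is why item 3 is needed.

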## 3. Discussion

This study aims to develop standardized, individualized, semi-supervised, in-bed, and self-exercise protocols and to investigate the feasibility and safety in patients with stroke.

Previous studies have shown a dose-dependent relationship between the intensity of rehabilitation therapies and functional recovery in stroke patients, particularly in walking ability, walking speed, and extended activities of daily living [43–45]. However, owing to the limited resources in the hospital rehabilitation system, it is difficult to achieve the optimal dose.

In-bed self-exercises based on EMG sensor feedback can be a good option for enabling stroke patients to perform the exercises with intermittent supervision. These exercises can be adjusted according to the goal achievement and improvement of function and muscle strength. In addition, they can provide stroke patients with objective and accurate information during practice to induce self-modification of behaviors, increase the rate of motor learning, and improve the time efficiency of therapy [46, 47]. To clarify the exercises description based on the proposed framework developed in a previous study, the exercises results in this study will be described with respect to the type, dosage, duration, intensity, and body positions, as well as the participation scale, rate and duration of exercises performance, and rate of goal achievement. In-bed self-exercises based on EMG-sensor feedback and supervision enable exercises with high dosage and intensity, along with a low fall risk for stroke patients with limited medical resources.

In this study, the PRPS is implemented as the primary outcome to assess patient engagement in in-bed self-exercises based on the EMG activities, addressing the absence of direct supervision by physical therapists. It categorizes patient participation into three types of exercise sessions, including participating, effortful, and successful sessions, which are defined by the number and percentage of contractions of target muscles and EMG amplitude of target muscles during contractions in this study. This approach allows physical therapists to evaluate the degree of patient participation in in-bed self-exercises quantitatively and to aid in planning the dose and intensity of future sessions without direct supervision. Using PRPS measurements based on EMG activities can be beneficial to assess patient participation in various forms of self-rehabilitation where therapist involvement is minimal.

The multicenter setting of this study may lead to potential inconsistencies between sites with respect to outcome assessments and exercises instructions. To mitigate this issue, careful monitoring and standardization of assessment techniques along with exercises instructions will be necessary. The research group will coordinate training sessions to implement proper assessment techniques and standardization at both study sites and hold regular meetings to maintain adherence to standard operating procedures.
